### Outcome measures in the SWELE program

#### Primary outcomes

After participated the SWELE program, the primary outcomes include reducing anxiety symptoms, reducing negative emotions, improving social skills in peer relationships; and changing in playfulness level among SEN children and adolescents.

For objective (1), to increase over 80% of SEN students’ happy mood after participated the SWELE program.

For objective (2), to reduce over 80% of SEN students’ anxiety symptoms (negative emotions) after participated the SWELE program.

For objective (3), to improve over 80% of SEN students’ social skills in peer relationships after participated the SWELE program; and.

For objective (4), to improve over 70% of the SEN students’ playfulness level after participated the SWELE program.

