### Population

Grade 1- Grade 12 SEN students (children and adolescents) will be enrolled from six selected special schools in Hong Kong. Inclusion criteria of study participants are: 1) students are studying in a special school; 2) students can speak and understand Cantonese; 3) students have no diagnosis of any cardiovascular disease; 4) parental consent obtained. Exclusion criteria of the study are: 1) students are not studying in the special schools; 2) students do not speak and understand Cantonese or English; 3) student has diagnosis of cardiovascular disease; 4) student cannot provide parental consent.

There will be 1,063 children and adolescents aged 6–18 years old with mild to moderate physical and intellectual disabilities (ID) from the six selected special schools will be recruited to participate the SWELE program implemented by the research team (Fig. 1). Based on our team’s experience, it is anticipated that at least 90% of them are eligible and willing to join the program, and the attrition rate would be less than 10%. It is therefore expected to have at least 850 children completing the program and outcome assessments. Such a sample size (*n* = 850) allows to detect a change in an outcome of effect size as small as 0.1 with 80% power at a level of significance of 0.05 (2-sided). An effect size of 0.1 is conventionally regarded as small [17].

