### Statistical analysis

Appropriate descriptive statistics, such as mean (standard deviation), median (inter-quartile range) and frequency (percentage) will be used to summarize and present the baseline characteristics and outcome data of the participants. Normality of continuous variables will be assessed based on their skewness and kurtosis statistics, values within ± 2 indicating the plausibility of normal distribution [19]. Suitable transformations will be made on skewed variables before subjecting them into inferential analysis. Paired sample t-test will be used to compare the change of each outcome (mood, anxiety, social, playfulness) at post-test with respect to pre-test within group and subgroups (age and gender). All statistical analyses will be performed using IBM SPSS 28 (IBM Crop., Armonk, NY) with level of significance set at 0.05.

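### The numeric targets under Primary outcomes (over 80% or over 70%) are not what the planned paired t-test or the power statement addresses

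*Protocol article*

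**What the plan says.** All places are in the protocol article.

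- **Objectives** lists four directional aims (mood up, anxiety down, self-regulation and social skills better, playfulness up) without any threshold.
- **Primary outcomes** opens directionally, then attaches a number to each objective: "For objective (1), to increase over 80% of SEN students", "For objective (2), to reduce over 80% of SEN students", "For objective (3), to improve over 80% of SEN students" and "For objective (4), to improve over 70% of the SEN students". The sentences go on to name happy mood, anxiety symptoms, social skills with peers and playfulness level.
- **Statistical analysis** names one inferential method: "Paired sample t-test will be used to compare the change of each outcome (mood, anxiety, social, playfulness) at post-test with respect to pre-test", overall and in age and gender subgroups, with "level of significance set at 0.05". Percentages appear there only among the descriptive summaries.
- **Population** says that 850 completers "allows to detect a change in an outcome of effect size as small as 0.1 with 80% power", two-sided at 0.05.

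No section says when a student counts as improved, compares a percentage with 80% or 70%, or gives power for such a comparison.

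**The concern.** A target of over 80% and a test of mean change against zero are different quantities. The t-test asks whether the average moved. It does not ask how many students moved, or whether scores moved by a given percentage. The article therefore carries two versions of its objectives, one directional and one numeric, and does not say which decides the conclusion.

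The abstract's Discussion expects the evaluation to confirm the objectives set in advance. With 850 students a very small mean change is significant, so all four outcomes could reach p < 0.05 and be reported as confirming the objectives while all four numeric targets were missed.

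**Working it through.** **Inputs.** From Population: 1,063 students, at least 90% eligible and willing, attrition under 10%, n = 850, effect size 0.1, 80% power, two-sided 0.05. From Primary outcomes: 80%, 80%, 80% and 70%. From Methods: mood item 1 to 5; STAI-6 total stated as 6 to 24, with six items answered on a 1 to 5 scale.

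**1. The plan's own figure.**
- Completers: 1,063 × 0.9 × 0.9 = 861, consistent with at least 850.
- Pairs needed for 0.1: ((1.960 + 0.842)/0.1)² = 785, or 787 with the t distribution.
- Smallest effect detectable with 80% power at 850: (1.960 + 0.842)/√850 = 0.096.
- Power at 0.1 with n = 850: 83.0%.

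The power statement is correct and slightly conservative. It concerns a standardised mean change.

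**2. First reading: share of students improved.** Assume change scores are normal with no ties, with standardised mean d in the direction of improvement. The share improved is Φ(d).

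| Situation | d | Share improved |
|---|---|---|
| Smallest observed effect giving p < 0.05 at n = 850 (1.963/√850) | 0.067 | 52.7% |
| Effect named in Population | 0.10 | 54.0% |
| Needed for 70% | 0.52 | 70% |
| Needed for 80% | 0.84 | 80% |

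At d = 0.1 the t-test is significant about 83% of the time, while the chance that the observed share exceeds 70% or 80% of 850 independent students is essentially zero (below 10⁻²⁰). Ties on the five-point mood item would lower the share strictly improved, and a student who starts at 5 cannot improve.

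**3. Second reading: percentage change in score.**
- STAI-6 on the stated range: the largest fall is (24 − 6)/24 = 75%.
- STAI-6 if six items scored 1 to 5 give 6 to 30: (30 − 6)/30 = 80% exactly. The article supports both ranges, and a fall of over 80% is impossible on either.
- Mood: a rise of over 80% that ends at 5 or below needs a baseline under 5/1.8 = 2.78, so only 1 or 2 on a single item. From 3 the score would have to exceed 3 × 1.8 = 5.4.
- Playfulness: 23 five-point items, if scored 1 to 5 with higher meaning more playful (an assumption), give 23 to 115. A rise of over 70% is then possible from 67 or lower (115/1.7 = 67.6).
- Social skills: the article gives no item response scale for the CBRS, so no limit can be worked out.

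The t-test against zero change tests neither reading.

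**4. What meeting a target would take at n = 850, independent students.** The Wilson 95% lower limit exceeds the target p₀ when the count exceeds 850p₀ + 1.96√(850p₀(1 − p₀)).
- 80%: 680 + 1.96 × 11.66 = 702.9, so 703 (82.7%). An exact one-sided binomial test at 0.025 needs 704.
- 70%: 595 + 1.96 × 13.36 = 621.2, so 622 (73.2%). The exact test also gives 622.

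Positive correlation within the six schools would raise these counts.

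**The case against.** The fair defence is that the section headed Objectives is directional, so a paired t-test is a sensible match for it, and that the percentages are hopes which the descriptive tables can report. A definition of improvement for each scale could also sit in a fuller document that is not shown.

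Part of this stands. Three stronger readings that a reader might infer are not supported:

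- **That a significant result would show no objective was met.** A significant change in the right direction does address the directional aims. Only the numeric targets are left untested.
- **That 0.1 SD is the planned effect and the targets contradict it by a factor of five to eight.** Population derives the sample from the students available and then says what 850 can detect. That is a sensitivity limit. No expected effect is stated, and hoping for a larger one is not inconsistent with it.
- **That an 80% change in score is out of reach on every scale.** It is impossible for anxiety, but on the mood item it is possible from 1 or 2 (1 to 2 and 2 to 4 are both 100%). Playfulness depends on how it is scored, and social skills cannot be judged.

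The rest of the defence does not remove the point. The percentages stand under Primary outcomes, one for each numbered objective. The descriptive summaries do not say which share is counted and compare none with a target. The conflict is between things the article itself fixes, so it is not detail left to another document.

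**Conclusion.** The point holds for the numeric targets under Primary outcomes. Carried out exactly as written, the plan yields p-values that cannot show whether any of the four targets was met, on either reading of the percentages, and nothing states which version of the objectives governs the conclusion.

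On the share-improved reading the gap is wide: significance is likely when little more than half of students improve, against targets of 70% and 80%. That size rests on normal change scores without ties and on independent students. The STAI-6 ceiling rests only on the stated scoring. The sample size statement is sound for the quantity it concerns.

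**What to change.** Reconcile Objectives, Population, Primary outcomes and Statistical analysis so that they concern the same quantity.

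**Preferred.** Make mean pre-post change with a 95% CI the primary quantity for each scale. Remove the 80% and 70% figures as primary targets. Report the percentage improved as secondary, with a definition of improvement fixed in advance for each scale. The existing power statement then fits.

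**If the targets stay.** Say that they mean the share of students improved. Define improvement for each scale, including how students already at the scale limit at baseline are counted. Estimate the percentage with a 95% CI that allows for the six schools, and call a target met only if the lower limit exceeds it: about 703 to 704 of 850 for 80% and 622 of 850 for 70% if students were independent, more with clustering. Give power for that comparison. With the exact test and independent students, 80% power needs true shares of about 83.9% and 74.4%.

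**Cost.** A rewording and one extra table, with no new data. The targets, if kept, are much harder to meet than p < 0.05.

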### Data collection

#### Procedure for data collection for quantitative method

Prior to commencing the study, a briefing session will be delivered to the direct care staff in the school, school nurses and schoolteachers who will assist the participants to complete the questionnaire and demographic sheet with their understanding and behavioural observations.

The study will be conducted with the support of and in partnership with the special schools’ school principals, schoolteachers, school nurses and school social workers as they all play a critical role in supporting the social and emotional development of SEN children and adolescents in the special schools. This is a before and after intervention data collection for quasi-experimental and observational study.

Ethical approval form and parental consents will be obtained prior to implementing the SWELE program in the six selected special schools.

Pre-test data collection will be conducted prior to starting the intervention (a 16-week SWELE program) for target participants. The research team members, student helpers and school nurses will work with schoolteachers to implement 16 sessions (45–60 min per session) for 16 weeks. The details of the activities of this intervention as shown in Table 1 above. Post-test data collection will be conducted immediately after participated the SWELE -program.

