**Methods:**

This 16-week SWELE program focuses on combining unstructured outdoor play activities with mindfulness-based interventions to promote mental wellbeing among children and adolescents with SEN. Training workshops for schoolteachers, school principals, parents and student mental health ambassadors in each special school together with a 16-week SWELE program and each last 45–60 min. Unstructured play allows students the freedom to explore, create and discover without predetermined rules or guidelines. Outdoor unstructured play activities include naturally run, jump and move on a playground, riding a bike, climbing trees, playing tag, playing with blocks, colour, water play, and boxes. A convergent parallel mixed-methods design both with a quantitative measure using a single group pre- and post-tests quasi-experiment behavioural observational method to preliminarily evaluate the impact of SWELE Program on SEN children’s and adolescents’ mental wellbeing; and with a qualitative design to conduct eight focus group discussions including schoolteachers, school principals, parents, SEN students, school nurses from six selected special groups and to explore their perceptions and experiences after participated the SWELE program.

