**Table 1 Tab1:**
[figure not shown]
Project Milestones of a SWELE Program

**Table 2 Tab2:** A 16-week SWELE program – extracurricular activities to promote SEN children’s and adolescents’ mental wellbeing status

SWELE Activities for age-appropriate groups /classes	Frequency/Schedule	Venue
(Training of Trainers) Training Workshop for Scout Leaders, School Nurses and Schoolteacher	One Whole Day	School Hall/Classroom
Training Workshop for Youth Mental Health Ambassador Program (SEN Students)	One Whole Day	School Hall/Classroom
Seminar for parents, school social worker, school nurses	Half a Day	School Hall/Classroom
Outdoor playground age-appropriate activities / games (using natural and recycle materials: branches, tyres, sand, water, leaves, boxes, plastic bottles, tools/toys…) Tunnel-through-boxes, Tyres Sand and water play, Tree House & Adventure Course Wobbly Wood Oasis Hut Merchant Play Ship with Pirate Tower. Play Ship Nina Sky climber with Artwork	35 min each time and 2 times per week for 16 weeks	School playground
Indoor mindfulness interventions	10 min each time and 2 times per week for 16 weeks	School Hall/Classroom: Storytelling, soft music, video, mindful arts
Mental Health Campaign	Once a month for four times	Games, smiling stickers, posters, emoji
‘Grow Your Mind’ Award with Certificate	One time only	Identify strengths on students and teacher-focus on connect, succeed, thrive and how this enable them to be productive and life-long learners

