### Main activities of SWELE program:

Unstructured outdoor free play integrated into the school’s extra-curricular activities (Youth Mental Health Ambassadors) to promote SEN students’ mental health for objectives 1–4.Use mindfulness-based podcasts, mindfulness games, mindfulness art for objectives 1–2.Through meditation and deep breathing technique, storytelling with relaxing waves piano music, yoga and mindful art for objectives 1–2.Training Workshops (Training of trainers) for Scout Leaders who will implement SWELE program in each special school.Youth Mental Health Ambassador Program for SEN students who are enrolled in Scout Club in each special school; SWELE training workshops for parents and schoolteachers will also be held in each special school for objectives 1–4.Examples of unstructured play might be creative play alone or with others, including artistic or musical games. imaginative games – for example, making cubbyhouses with boxes or blankets, dressing up or playing make-believe, exploring new or favorite spaces like school backyards, parks, playgrounds and so on.

The key milestones to implement the SWELE program can be found in Table 1. The SWELE program is a 16-week program and the main activities include: One training workshop for three groups in each special school: 1) Scout Leaders (special schools’ teachers), 2) SEN students (scouts in the school) to become Youth Mental Health Ambassadors and 3) for parents, school social workers, school nurses, schoolteachers and stakeholders; 45 min unstructured outdoor play with mindfulness activities two times per week for 16 weeks (see Table 1 below).

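### The text implies, without stating it, that staff are trained between pre-test and post-test, so a change in how raters use the scales could pass for student change

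*Protocol article*

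**What the plan says.** Under the procedure for quantitative data collection, the baseline is fixed relative to the program: "Pre-test data collection will be conducted prior to starting the intervention (a 16-week SWELE program) for target participants". The second measurement follows it: "Post-test data collection will be conducted immediately after participated the SWELE -program".

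Two places put staff training inside that program. Table 2, titled "A 16-week SWELE program – extracurricular activities to promote SEN children’s and adolescents’ mental wellbeing status", has as its first row a one-day event: "Training of Trainers) Training Workshop for Scout Leaders, School Nurses and Schoolteacher". The section on main activities says: "The SWELE program is a 16-week program and the main activities include: One training workshop for three groups in each special school". It identifies the first of those groups as the schools' own teachers ("1) Scout Leaders (special schools’ teachers") and links workshops for parents and teachers to all four objectives.

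One staff step is placed ahead of the study: "Prior to commencing the study, a briefing session will be delivered to the direct care staff in the school, school nurses and schoolteachers". That briefing is for the people who help complete the questionnaires, and it is a separate item from the workshop.

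The design is a single group measured twice (Trial design), and each outcome is compared by a paired t-test (Statistical analysis).

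**The concern.** If the pre-test comes before the program and the workshop belongs to the program, staff rate students once before and once after a full day of training. Training can change what a rater notices and where a rater places a given behaviour on the scale, even if the student behaves exactly as before. The protocol's own rationale makes this plausible: the Background and Discussion say that free play and its benefits are widely misunderstood, including by parents.

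Such a shift adds to the change of every student rated by a trained rater. Its average goes straight into the mean change, and a larger sample does not reduce it. No control group is rated by the same staff over the same interval, so the analysis cannot remove it. The Discussion acknowledges a placebo effect, to be explored qualitatively. A change in the raters' standard is a different problem and is not mentioned.

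**Working it through.** **Step 1: order of events, from the text.**
- Workshop within the program: Table 2 (title and first row) and the main activities section.
- Pre-test before the program: procedure for quantitative data collection.
- Post-test after the program: same section.
- Implied order: briefing, pre-test, workshop, student sessions, post-test. The workshop falls between the two ratings. This is an inference from three places, not a stated schedule.

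**Step 2: do the raters attend the workshop?**
- Self-regulation and social skills (CBRS): teacher report. Teachers are among those trained, so the overlap is clear, although nothing says that every rating teacher attends.
- Anxiety (STAI-6): answered by observers who are not further identified. Nurses, teachers and direct care staff help complete the forms. Overlap is probable.
- Playfulness (CPS): rater not fixed, and a parent version is described. There is overlap if staff rate it. If parents rate it, the half-day parent seminar in Table 2 raises the same question.
- Mood (Emoji Mood Scale): student self-report with staff assistance. Least exposed.

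**Step 3: the protocol's own sample-size figure (Population section).**
- Inputs: 1,063 students, at least 90% joining, less than 10% attrition, n = 850, effect size 0.1, 80% power, two-sided 0.05.
- Completers: 1,063 × 0.9 × 0.9 = 861, consistent with at least 850.
- Detectable standardised change in a paired design: (1.960 + 0.842)/√850 = 2.802/29.15 = 0.096, which rounds to the stated 0.1. At exactly 0.1, power is 83%. The statement is sound and slightly conservative.

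**Step 4: how small a shift matters.**
- Smallest observed change reaching p < 0.05: t(0.975; 849 df)/√850 = 1.963/29.15 = 0.067 SD of the change score.
- Now assume no true student change and a mean rater shift d, in SDs of the change score. The chance of a significant paired t-test at n = 850 (noncentral t, noncentrality d√850) is:
  - d = 0: 5%
  - d = 0.05: 31%
  - d = 0.07: 53%
  - d = 0.10: 83%
  - d = 0.15: 99%
  - d = 0.20: over 99.9%

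The values of d are assumptions; the documents give no estimate of any rater shift. The calculation treats students as independent, as the planned test does.

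**The case against.** The strongest reply is that the order is not stated. The pre-test sentence ends by referring to target participants, who are the students, so it may require only that students be measured before their own sessions start. The abstract sets the workshops beside the program rather than inside it: "in each special school together with a 16-week SWELE program". Scout leaders who will deliver the program must be trained before delivery, but that could be before or after the pre-test. Table 1, the milestone table, may settle the order and is not shown. All of this stands. A reader might infer that the protocol schedules training after the pre-test. It does not say so, and the point is only that its wording implies that order and nothing visible fixes the other one.

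A reader might also infer that every outcome is affected whoever the rater is. The documents do not support that: the mechanism needs a rater who attended the workshop, and Step 2 shows clear overlap only for the CBRS.

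Nor is there evidence that a shift will occur, or in which direction. Table 2 gives the workshop's title, audience, length and venue, not its content. Converting 0.1 SD into CPS points with an assumed SD would only restate the design target in other units, and on a scale whose rater is open.

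Finally, reordering is a partial remedy. Teachers and nurses help run the sessions for 16 weeks, and their standards may drift in that time. If the workshop counts as intervention, a later pre-test is also no longer wholly pre-intervention. Both points stand and limit what the change can achieve.

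**Conclusion.** The point holds in limited form. The text makes the whole-day staff workshop part of the program and puts the pre-test before the program. The implied order therefore places training between the two ratings. For outcomes rated by staff who attend (CBRS, probably STAI-6, and CPS if staff rate it), any training-induced change in scale use cannot be separated from student change in this single-group comparison.

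The size and direction are unknown. What can be said is that the margin is narrow: about 0.067 SD of observed change is significant at n = 850, and an assumed pure rater shift of 0.10 SD would give significance 83% of the time. This conclusion rests on Table 2 and the main activities section defining what the program contains, and on raters being among those trained. It would fall away if Table 1 or the full protocol places the workshop before the pre-test. The sample-size statement itself is not in question.

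**What to change.** In the procedure for quantitative data collection, state the order for each school, in both batches:
1. rater briefing;
2. staff training workshop, and the parent seminar if parents rate the CPS;
3. pre-test, within a few days;
4. student ambassador workshop and student sessions;
5. post-test.

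Name who rates the CPS and who the STAI-6 observers are, so that it is clear which raters must be trained before baseline. If this order is already intended, one sentence saying so is enough.

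The cost is small: planned steps are reordered, with no added visits or staff. Any effect of trained staff on students in the few days before the pre-test would not be counted. Rater drift and expectancy during the 16 weeks of delivery are not removed, and the protocol should state them as a limitation of the staff-rated outcomes.
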